##### HF Symptoms and Performance Status

Study participants’ symptoms and performance status will be evaluated using the Kansas City Cardiomyopathy Questionnaire (KCCQ-12) at 0, 3, and 6 months (Multimedia Appendix 1), with absolute results and change over study duration reported.

##### HF Clinical Events

The study’s primary clinical end point is HF hospitalizations. Secondary clinical events include other unplanned hospitalizations and ED visits. Clinical events will be obtained through monthly electronic health record review by the research team and with monthly patient surveys. All hospitalizations will be adjudicated by the clinical team as either HF or other unplanned hospitalizations. Clinical end points will be compared to those of matched controls.

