## Methods

### Overview

The Nov-RPM-HF trial is a single-center prospective study of an RPM platform and its adoption, clinical utility, and ability to optimize GDMTs and reduce unplanned acute care events among patients with HFrEF. Specifically, the trial will evaluate patient adherence with passive and active data collection, patient-perceived usability and utility of the RPM platform to monitor their health status, clinician-perceived usability and utility of the RPM platform for HF management, clinical utility of the RPM clinical alerts, impact of RPM on medication changes and titration of HF GDMT, and impact of HF RPM on clinical outcomes (ED visits, hospitalizations).

Full inclusion and exclusion criteria are summarized in Textbox 1. Inclusion criteria include history of HFrEF with a HF hospitalization or ED visit in the last 12 months. This criteria selects for a HFrEF population with a baseline event rate that mirrors the trial population in the CHAMPION (CardioMEMS Heart Sensor Allows Monitoring of Pressure to Improve Outcomes in NYHA Class III Heart Failure Patients) trial. Such an event rate should allow for increased power to detect clinical outcomes among our study population. Prior noninvasive RPM trials have included a relatively stable population of patients with HF with low clinical event, and this was thought to have contributed to the inability to demonstrate clinical efficacy [13]. End-stage HF with a life expectancy <1 year or requiring advanced therapies including left ventricular assist devices or cardiac transplantation were excluded. Patients with barriers precluding them from obtaining monitored data (eg, wearable defibrillator use preventing ballistocardiograph sensing) were also excluded.

Inclusion and exclusion criteria.

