### Study Protocol

Following enrollment, study participants have the Home Hub and sensors shipped to their homes. Once the kit is delivered, the technical support team will reach out to assist with home monitoring and sensor setup.

As part of the study, patients will take measurements daily from all study sensors. The first 7 days for each patient will be a run-in period where patient data is collected. If sufficient data is collected and transmitted, study participants will transition to the active management phase. Sufficient data is defined as transmission from both BP cuff/weight scale and ballistocardiograph sensors in at least 4 of the 7 days. If minimum requirements are not met, patients are continued in the run-in period for an additional week (up to 3 weeks maximum). Technical support will contact patients to determine if lack of transmission represents a technical issue versus nonadherence. If patients were unable to meet minimum data requirements after 3 weeks, then they were disenrolled from the study.

Following run-in period completion, study participants will enter the 6-month active management phase of the study. A designated research nurse is responsible for daily monitoring of the RPM clinical interface. This includes monitoring the RPM clinical interface daily for clinical alerts, contacting patients to assess clinical status in response to alerts, and escalating to the patient’s HF cardiologist if clinical status warrants management changes. This research nurse will also be responsible for contacting study participants for issues with data transmission or poor adherence to patient data collection.

On a monthly basis, enrolled patients will have their clinical data reviewed by a multidisciplinary team including a triaging nurse and an HF cardiologist. The purpose of these reviews is to assess participant’s clinical status and adherence to data transmissions, and to identify opportunities for optimized medical management, including maximizing GDMT. RPM platform monitoring is outlined in Figure 2.

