#### Statistical Analysis

Patient medication changes and clinical events will be compared to 100 matched historical controls. Controls will be patients with HFrEF matched on an HF hospitalization in the past year, age within 5 years, sex, race, and comorbidities (coronary artery disease, diabetes mellitus, hypertension, renal disease).

Statistical analysis for clinical end points will be in comparison with matched controls. For survey data, including RPM platform utility and patient symptom assessments, these will be evaluated for change over the trial’s 6-month duration. Continuous variables will be assessed via sample *t* tests, and categorical variables will be assessed via chi-square tests.

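### HF admissions are compared with historical controls without death as an outcome or time at risk in the tests, so a favourable trend could not be read as benefit

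*Protocol article*

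**What the plan says.** Under HF Clinical Events the article states: "The study’s primary clinical end point is HF hospitalizations". It continues: "Secondary clinical events include other unplanned hospitalizations and ED visits". The Overview gives the same pair, ED visits and hospitalizations, as the clinical outcomes, and the Abstract names only unplanned HF hospitalizations or ED visits. Adjudication has two outcomes: "All hospitalizations will be adjudicated by the clinical team as either HF or other unplanned hospitalizations".

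The comparator is historical: "Patient medication changes and clinical events will be compared to 100 matched historical controls". The only tests named under Statistical Analysis are t tests for continuous variables and, for the rest, "categorical variables will be assessed via chi-square tests". Follow-up is fixed by design: "study participants will enter the 6-month active management phase of the study".

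Mortality appears only as background in the Abstract and Introduction. Limited life expectancy is an exclusion criterion. No section makes death an outcome or says how a patient who dies enters the comparison. Under Power Calculation, HF hospitalization is declared underpowered but is kept to see whether monitoring shows a favourable trend.

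**The concern.** Death ends the possibility of admission. A t test on counts or a chi-square test on proportions over a nominal 6 months gives full follow-up to a patient who died in month 1. If that patient had no HF admission, the group's result improves.

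Equal deaths would roughly cancel, but nothing in the design secures equality:

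- The controls are historical and not randomized.
- Participants must pass a data-transmission run-in of up to 3 weeks or be disenrolled. No matching filter is described for controls.
- Participants may qualify through an ED visit, whereas controls are matched on an HF hospitalization.
- NYHA class and ejection fraction are not among the listed matching factors.

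The tilt could go either way, hiding a harm or masking a benefit. At stake is the meaning of the planned trend. Fewer admissions with more deaths and fewer admissions with equal deaths would look the same in the listed clinical outcomes.

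**Working it through.** **The plan's own figure.** The article says 1054 patients per group would give 80% power for HF hospitalization. It gives neither the baseline rate nor the effect as a number, so the figure can be neither confirmed nor refuted. Solving n = (1.960 + 0.842)² (λ₁ + λ₂)/(λ₁ − λ₂)² for n = 1054 (two-sided 0.05 assumed) fits control rates of about 0.34, 0.61 or 1.41 for rate ratios of 0.80, 0.85 or 0.90. At 100 per group, power is Φ(√(100/1054) × 2.802 − 1.960) = Φ(−1.10), about 14%. This agrees with the article's statement that the end point is underpowered.

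**Inputs for the check.** Six months of follow-up, 100 per group and tests without a time element come from the article. Admission and death rates are not given and are assumed: 20-40% with an HF admission in the absence of death, and 5% versus 2% deaths. The higher death risk is put in the monitored group for illustration only. The admission hazard is the same in both groups, so the true effect is nil.

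**Formulas.** With constant 6-month hazards λ (admission) and μ = −ln(1 − death risk):

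- Observed proportion with an HF admission = λ/(λ + μ) × (1 − e^−(λ+μ))
- HF admission or death = 1 − e^−λ × (1 − death risk)

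**One case worked, λ = 0.30.**

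- 5% deaths: μ = 0.0513. Admission: 0.30/0.3513 × (1 − e^−0.3513) = 0.854 × 0.2962 = 25.3%. Composite: 1 − 0.7408 × 0.95 = 29.6%.
- 2% deaths: μ = 0.0202. Admission: 0.30/0.3202 × (1 − e^−0.3202) = 0.9369 × 0.2740 = 25.7%. Composite: 1 − 0.7408 × 0.98 = 27.4%.
- Risk ratios: 0.985 for admission and 1.08 for the composite.

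**Range at 5% versus 2% deaths.**

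| Admitted if no deaths | λ | HF admission | Shift (points) | RR | Admission or death | RR |
|---|---|---|---|---|---|---|
| 20% | 0.223 | 19.5% vs 19.8% | 0.29 | 0.985 | 24.0% vs 21.6% | 1.11 |
| 30% | 0.357 | 29.3% vs 29.7% | 0.43 | 0.986 | 33.5% vs 31.4% | 1.07 |
| 40% | 0.511 | 39.1% vs 39.6% | 0.56 | 0.986 | 43.0% vs 41.2% | 1.04 |

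**A wider gap.** With 10% versus 5% deaths and λ = 0.30, HF admission is 24.7% versus 25.3% (RR 0.975) and the composite is 33.3% versus 29.6% (RR 1.13).

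**If frailer patients are both admitted and die more.** With gamma frailty of variance 1 and mean rate 0.30, 10% deaths cut the mean count from 0.30 to 0.27, about 10%. Without frailty the same deaths cut it to 0.285, about 5%.

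**What person-time does.** Without frailty, mean time at risk is (1 − e^−μ)/μ, which is 0.05/0.0513 = 0.975 and 0.02/0.0202 = 0.990 of the 6 months. Mean counts are 0.292 and 0.297. Dividing gives 0.30 in both groups, so the tilt disappears. With frailty it need not disappear fully, so deaths should be reported as well.

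**The case against.** The strongest reply is that the article is a condensed text. Rules for deaths and censoring commonly sit in an analysis plan, and the Poisson assumption under Power Calculation shows that the Statistical Analysis section is not the full specification. That stands for the handling rule: the article never says a dead patient is scored as event-free, and that reading is an inference from the tests it names. It does not remove the point, because the article itself states the list of outcomes and the tests, and the Abstract, Overview and HF Clinical Events sections all leave death out.

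Several limits also stand:

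- A patient who dies during or after an HF admission is still counted.
- Unequal deaths are needed for any tilt.
- Excluding hospice care, life expectancy under 1 year, advanced therapies and dialysis lowers the expected number of deaths.
- The tilt is small against chance. At 30% admitted, 0.43 points compares with an unpaired standard error of √(0.293 × 0.707/100 + 0.297 × 0.703/100), about 6.4 points.
- A split of 5 versus 2 deaths per 100 is itself compatible with chance (Fisher p = 0.44).

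A reader might infer two stronger things. One is that a few excess deaths would swamp the planned comparison: with 30% admitted and an assumed 15% reduction, the benefit is 4.5 points, and 3 extra deaths per 100 is two thirds of that. That ratio describes the composite. The distortion of HF hospitalization itself is 0.43/4.5, about a tenth. The other is that harm from the strategy would appear nowhere. Non-fatal harm can appear as other unplanned admissions, ED visits, actions on low blood pressure or heart rate alerts, or KCCQ scores. Only death itself has no listed outcome.

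**Conclusion.** The point holds in a limited form. As written, the clinical comparison omits death and uses tests that ignore time at risk, so deaths before a first HF admission favour the group in which they are more frequent. Under the assumed rates the bias in HF hospitalization is about 0.3-0.6 percentage points at 5% versus 2% deaths. It is somewhat larger with a wider gap in deaths or with frailty. It is nil if deaths are equal.

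The bias alone would not change a decision. What matters is interpretation: with about 14% power, non-randomized controls and a plan to read a trend, the admission result and the result including deaths can point in opposite directions, and the listed outcomes would show only the first. All death and admission rates here are assumptions, since the article gives none. This is a cheap improvement to an exploratory end point and no threat to a confirmatory claim.

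**What to change.** 1. Add all-cause death to the list under HF Clinical Events, ascertained over the same 6-month window and from the same type of source in participants and controls.
2. Analyse HF hospitalizations as a rate per person-month at risk, with follow-up ending at death.
3. Report the number of deaths, and HF hospitalization or all-cause death, beside HF hospitalization in both groups, labelled exploratory.
4. State that a trend in admissions will be interpreted only together with the deaths.

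The cost is a little more data extraction and one extra analysis, with no change to recruitment or to the intervention. Two drawbacks should be stated. Deaths outside hospital may be under-recorded in historical controls, which would bias the composite and belongs among the limitations. The composite may also show a smaller effect than admissions alone.

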**Methods:**

Nov-RPM-HF is a 100-patient single-center prospective trial, evaluating patients over 6 months. The outcomes will include patient adherence to data collection, patient/clinician-perceived utility of the RPM platform, medication changes including the titration of guideline-directed medical therapy to target doses, heart failure symptoms/performance status, and unplanned heart failure hospitalizations or emergency department visits.

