#### Clinical Alerts and Thresholds

Several clinical monitoring alerts will be used prospectively during the management phase of the study. Each alert has default thresholds that are customizable to individual study participants. Absolute threshold alerts will be turned on by default in all patients, while GDMT alerts can be opted-in by the clinical team for patients deemed to be on submaximal GDMT. Default values are shown in Textbox 2. All alerts are required to be addressed within 24 hours by the monitoring nurse and escalated to the clinical team if indicated. Actions taken by the clinical team in response to the alerts were documented.

Remote patient monitoring clinical interface parameters with default values.

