##### Medication Changes

Clinician-directed changes will be tracked during trial duration for the following HF medication classes: beta-blockers, angio-converting enzyme (ACE)/angiotensin receptor blocker (ARB)/angiotensin receptor-neprilysin inhibitors (ARNIs), magnetic resonance angiographies (MRAs), hydralazine, nitrates, and loop diuretics. The distance to target dose will also be assessed for GDMT medications, beta-blocker, ACE/ARB/ARNI, and MRA drug classes. Based on previously established methodology [10], baseline doses of each of these drug classes will be the classified percentage of target dose: 0% to 25%, 25% to 50%, 50% to 75%, and 75% to 100%. This target dose category will be compared for each participant between 0 and 6 months to assess for changes in GDMT dosing. Change in proximity to target dose over trial duration will be compared to that of matched controls (see “Statistical Considerations” for matching methodology). For all drug classes, the absolute number of medication changes will be recorded and compared to that of the matched controls.

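### Participants' clinical events come partly from monthly surveys that historical controls cannot have completed, so HF hospitalizations and ED visits are not captured alike in the two groups

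*Protocol article*

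**What the plan says.** The HF Clinical Events section of the protocol article defines the end point: "The study’s primary clinical end point is HF hospitalizations". Other unplanned hospitalizations and ED visits are secondary. The same section fixes the sources, "Clinical events will be obtained through monthly electronic health record review by the research team and with monthly patient surveys", the classification, "All hospitalizations will be adjudicated by the clinical team as either HF or other unplanned hospitalizations", and the use, "Clinical end points will be compared to those of matched controls".

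The Statistical Analysis section identifies the comparator: "Patient medication changes and clinical events will be compared to 100 matched historical controls". The abstract gives the size and length of follow-up: "Nov-RPM-HF is a 100-patient single-center prospective trial, evaluating patients over 6 months".

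The Clinical Alerts and Thresholds section describes what else the clinical team does. The monitoring nurse escalates alerts to it, and "Actions taken by the clinical team in response to the alerts were documented".

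Under Power Calculation, HF Hospitalizations, the article calls the trial underpowered for this end point. It gives 1054 patients and 1054 controls as the number needed for 80% power, and says the end point will be collected anyway to see whether a favourable trend appears.

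**The concern.** One of the two stated event sources exists in one group only. Admissions to the study hospital should appear in its record for both groups. Events elsewhere may be missing from that record, and there the monthly survey is what brings them to light. It does so for participants alone. Participants' counts then rise relative to controls' for a reason unrelated to monitoring, so a real reduction can look smaller or vanish, and no effect can look like harm.

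The HF label is a second and separate matter. The end point depends on it, and it is assigned by a team that knows who is monitored and responds to the alerts. The article states neither masking nor how control hospitalizations are classified, so the two groups' labels need not mean the same thing.

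**Working it through.** **The plan's own figure.** The 1054 per group cannot be rebuilt, because the article prints neither the baseline rate nor the effect size. It can be solved backwards. Take a two-sided 5% Wald test of a Poisson log rate ratio, with λ the control events per patient over 6 months (assumed) and RR the rate ratio:

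- SE = √[1/(1054λ) + 1/(1054λ·RR)]
- power = Φ(|ln RR|/SE − 1.96) = 0.80

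For λ from 0.2 to 0.6 this gives RR from about 0.74 to 0.85. With 100 per group the same effects have about 14% power, which agrees with the article's statement that the end point is underpowered. The figure is not in dispute. It only shows the size of effect the authors had in mind.

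**Unequal capture.** Let s be the share of true events known only from a survey, assumed equal in both groups. If every such event is counted in participants and none is recovered in controls:

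- participants' observed rate = λ·RR
- controls' observed rate = λ(1 − s)
- apparent ratio = RR/(1 − s)

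Both s and the true ratio of 0.85 are assumptions; 0.85 is the milder end of the back-solved range.

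| s (assumed) | true 1.00 reads as | true 0.85 reads as |
|---|---|---|
| 10% | 1/0.90 = 1.11 | 0.85/0.90 = 0.94 |
| 15% | 1/0.85 = 1.18 | 0.85/0.85 = 1.00 |
| 20% | 1/0.80 = 1.25 | 0.85/0.80 = 1.06 |
| 30% | 1/0.70 = 1.43 | 0.85/0.70 = 1.21 |

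**Effect on the test.** With no true effect and 100 per group, SE = √[1/(100λ(1 − s)) + 1/(100λ)]. For s = 20% and λ = 0.3, SE = √(1/24 + 1/30) = 0.274 and ln(1.25)/SE = 0.81, so the two-sided rejection rate is about 13%. For λ = 0.6, SE = √(1/48 + 1/60) = 0.194, the ratio is 1.15, and the rate is about 21%. Both stand against a nominal 5%, and the excess lies in the direction of harm. For s = 10% the rates are about 7% to 9%.

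**Labelling.** Let m be the share of participants' HF hospitalizations labelled as other, beyond any such share in controls. The apparent ratio becomes RR(1 − m)/(1 − s). With s = 0 and RR = 1.00, m = 10% or 20% gives 0.90 or 0.80, a spurious favourable trend. Labelling that leans the other way pushes the ratio above 1. With s = 20% and m = 20% the two errors happen to cancel, (1 − 0.20)/(1 − 0.20) = 1.00, but nothing in the plan makes that likely.

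**The case against.** **The end point is declared underpowered.** This is true and limits the consequence. With 100 per group and λ of 0.3 to 0.6, the 95% interval multiplies or divides the rate ratio by exp(1.96·√(2/30)) = 1.66 down to exp(1.96·√(2/60)) = 1.43. A shift to 1.11 lies well inside that. What remains is that a trend will still be read from this comparison, and that unequal capture is a bias which the wide interval does not describe and more patients would not remove.

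**The control data source is not stated.** It would go too far to say that controls have health-record data only, since the article names no source for them and a fuller document may. The narrower statement holds: historical patients cannot have answered this trial's monthly surveys.

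**A survey report may only prompt retrieval of records.** The article does not say that an unverified report counts as an event. Verification would remove false reports, but a confirmed outside admission would still have been found through a route closed to controls.

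**The size is assumed.** This stands in full. No survey-only share appears in the documents.

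**A reader might extend the point to medication changes**, supposing that a nurse tracks them prospectively in participants while controls rely on charts. The article does not support this. It says "Clinician-directed changes will be tracked during trial duration for the following HF medication classes" and names neither a tracker nor a source. The research nurse's described work is monitoring, contact and escalation, and alert-triggered actions are reported as a separate outcome. Participants' changes may come from the same chart source as controls'.

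**A reader might also infer that each patient's own clinicians judge that patient's events.** The text says only the clinical team. The alerts section shows that this team acts on alerts, but not who within it classifies events, nor who classifies control events.

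**Conclusion.** The point holds for clinical events. As written, the plan finds participants' hospitalizations and ED visits by two routes, at least one of which is closed to historical controls, and it states no common rule to offset this. The resulting bias runs against remote monitoring. Unmasked HF labelling is a secondary weakness whose direction is unknown, so the net bias on HF hospitalizations cannot be signed.

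The size is unknown. The illustrative ratios of 1.11 to 1.43 rest on assumed survey-only shares of 10% to 30%, full counting of those events in participants and none in controls. If some are unverified in participants or recovered in controls, the shift is smaller.

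This is a should-fix. It affects what the article names as its main clinical end point and a trend it intends to interpret, but the article does not present that comparison as confirmatory.

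**What to change.** 1. For the comparison of hospitalizations and ED visits with controls, count only events found by one written health-record abstraction rule applied to both groups over equal 6-month windows. Have the rule exclude events known only from a study survey or a monitoring contact note. Otherwise the extra contact with participants could bring outside events into the chart and restore part of the asymmetry.
2. Report participants' survey-only events separately, outside the comparison.
3. Classify HF versus other by one fixed rule for both groups, for example principal discharge diagnosis. If judgement is kept, use discharge records with monitoring and alert content removed.
4. Show all unplanned hospitalizations beside HF hospitalizations. That total needs no HF judgement and can be formed from events already planned for collection.
5. As a precaution, state that medication changes are counted from the same chart source in both groups.

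The cost is a few sentences of protocol or SAP text and a shared abstraction form, plus some work if records have to be redacted. The main loss is that some genuine participant events leave the comparison, so precision falls a little. No new data collection from patients is needed.
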